### Recruitment

In order to have a sufficient (to improve generalisability) but reasonable (for convenience reasons) number of GPs involved, all participating GPs caring for at least three eligible residents were identified. If possible, a maximum of 12 GPs per NH was aimed for. The objective was to include 35 residents per NH. One member of the research team performed resident selection assisted by the head nurse, the coordinating physician or a representative of the management board. An algorithm was developed (available upon request) to support NHR recruitment. If there were more than 35 eligible residents, a random selection was made using a statistical software (Statistical Package for the Social Sciences (SPSS) version 22). Written informed consent was asked by physicians (GPs or coordinating physicians) or nurses to each resident or to a resident’s representative if the resident was not mentally competent (e.g. in case of severe dementia). Due to practical reasons, resident inclusion could not be performed before group allocation.

### Intervention

Based on the evidence that the most successful interventions tend to be interdisciplinary and include more than one method [15, 17, 18, 26], a multifaceted strategy was chosen. The key element of this complex intervention is the structured and repeated interdisciplinary resident’s medication review (referred to hereafter as ‘interdisciplinary case conferences’) supported by training and local concertation. Each component of the intervention is described hereafter and in Table 1. The timeline is provided in Fig. 2. The main components of the complex intervention have been tested during the pilot phase and were refined afterwards.

**Table 1 Tab1:** Intervention components

Intervention component	Description	Participants involved	Moment and frequency	Incentives
Training—e-learning	Module 1: Pharmacotherapy in older people; potentially inappropriate medications and tools used to measure it Module 2: What is a medication review? How can each health care professional contribute? Module 3: How to perform an interdisciplinary medication review? Module 4: Teamwork	Physicians Nurses Pharmacists	Available during whole study period	Accreditation for GPs and pharmacists; certificate of attendance for nurses
Training—onsite workshops	Specific training for pharmacists, provided by the research team: ▪ How to prepare a medication review? How to make a suggestion? Where to find relevant information about medications?	Pharmacists	At month 2	Accreditation for pharmacists
	Training for all HCPs, provided by the research team: ▪ Problem-based learning using clinical vignettes: How to conduct an interdisciplinary medication review? What is the contribution of each HCP? How to classify DRPs?	Physicians Nurses Pharmacists	At month 2	Accreditation for GPs and pharmacists; certificate of attendance for nurses
	Specific training for nurses, provided by the coordinating physician and/or pharmacist: ▪ Detection of adverse drug events by nurses ▪ Drug administration	Nurses	Twice or more during the study period	Certificate of attendance
Local concertation	Discussion about the use of two classes of medications (antidepressants and lipid-lowering drugs) at the level of the nursing home	Physicians Nurses Pharmacists	Twice during the study (first at month 3 or 4)	Remuneration for all HCPs involved in the COME-ON study
Interdisciplinary case conferences	Face-to-face medication reviews for each included NHR; duration approximately 20 min	Physicians Nurses Pharmacists	Once per 4 months	Remuneration for all HCPs

*DRP*(s) drug-related problem(s), *GP*(s) general practitioner(s), *HCPs* health-care professionals, *NHR* nursing home resident

**Fig. 2 Fig2:**
[figure not shown]
Timeline of COME-ON intervention

### Component 1: education and training

A blended learning programme, combining e-learning with face-to-face workshops, has been developed. Training needs and desired formats were discussed during focus groups with HCPs. The structure of the e-learning platform, the format and content of the blended learning programme were developed in collaboration with a team of HCPs and experts in e-learning and geriatric pharmacotherapy.

The e-learning consists of four modules on the following topics: drugs and ageing; (in)appropriate prescribing; medication review; and team work. Each module takes approximately 60 min to complete and is built up from a variety of learning formats including narrative powerpoints, videos, serious games, assignments, summary tools on specific topics and tests. All participating HCPs from NHs allocated to the intervention group have access to the e-learning platform that is available during the whole study duration.

Educational material developed by the research team is also available through the e-learning platform. It includes a medication review flowchart, a shortlist of STOPP/START criteria, and summary sheets on different topics (e.g. renal function, anticholinergic drugs,…).

Furthermore, the research team moderates two types of face-to-face interactive workshops (i.e. onsite training), 2 h each, one specific for pharmacists and one with all participating HCPs of one or more NHs. The aim is to apply the theoretical concepts, addressed during the e-learning, to clinical cases, and to get familiar with research instruments (DRP classification; web application). Specific onsite training for nurses can be given by the coordinating physician and/or the pharmacist. To encourage this type of training, preparatory material on administration of medications and on detection of ADEs is provided by the research team.

As an incentive, the e-learning modules and onsite workshops are accredited for GPs as well as for pharmacists. As there is currently no similar accreditation programme for nurses, they receive a certificate of attendance.

### Component 2: local concertation

At the level of each participating NH, physicians (GPs and coordinating physician), pharmacists and nurses are asked to participate in two ‘local concertation’ meetings. The objectives of this component are (a) to reach consensus on the appropriate use of one specific class of medication within each NH, with the intent that this work could then be used during the interdisciplinary case conferences and (b) to initiate teamwork and communication between HCPs of the same NH. The overall output is expected to be (i) a ‘vision’ or a ‘management plan’ for the treatment of certain condition(s), (ii) a list of (in)valid indications for the use of the discussed medications; (iii) a list of molecules to be preferred or avoided, and underlying reasons and (iv) modalities of the use of the preferred drugs (e.g. dosage, duration, follow-up,…). Two medication classes—antidepressants and lipid-lowering drugs—were selected by the research team. Material to support the preparation of the meetings and the discussion is provided by the research team.

Each meeting is expected to last approximately 2 h. The coordinating physician, the pharmacist and the head nurse are invited to take the lead in preparing, organising and implementing the meetings (i.e. invitations, content, discussion, guidelines, overview of figures and numbers of NHRs taking these medications, summary, report). Depending on the opportunities and willingness, additional HCPs can be invited to participate (e.g. geriatrician, psychiatrist, physiotherapist, occupational therapist). The first meeting has to be held at the beginning of the study, ideally before the first interdisciplinary case conferences. A second meeting takes place several months later. The objective of the latter is to review the implementation of the consensus reached after the first meeting, to re-discuss or amend this consensus if necessary, and/or to start the discussion about the second medication class. The HCPs involved in the study are paid for their attendance at the meetings.

### Component 3: interdisciplinary case conferences

Face-to-face medication reviews have to be conducted for each NHR included in the study, by an interdisciplinary team consisting of three HCPs: the GP, the pharmacist, and a nurse (head nurse, or other nurse involved in the care of the resident). The medication review focuses on the appropriate and cost-effective use of all medications taken by the resident. During the discussion, the team determines whether drugs must be additionally prescribed, tapered, discontinued, dose-adjusted, or replaced, and whether other actions are needed. They are also requested to prioritise and time schedule the treatment modifications to be made. Drug-related problems and interventions must be recorded using a DRP classification tool adapted from Basger et al. [28] and from the PCNE classification V6.2 [29].

The interdisciplinary case conferences are facilitated by the use of a web application. This web application was primarily developed for allowing electronic data collection (clinical, medical, economic and medication data). It also enables (i) sharing data about NHRs between HCPs in the intervention group, allowing preparation of the medication review by each HCP and (ii) generating a standardised report of every case conference, including details on DRPs and interventions, with the possibility to re-discuss or amend these interventions at the next meeting.

A total of three case conferences per resident over a 12-month period are aimed for. Each case conference is estimated to last about 20 min. For residents with a hospital admission during the study period, HCPs are encouraged to perform an additional medication review in the fortnight after hospital discharge. For residents entering end-of-life care, an additional medication review can be conducted with a focus on stopping unnecessary medications and optimising comfort.

NHRs do not participate in the case conferences. However, the nurse and the GP are supposed to represent the interest of the residents by sharing information on the perception and preferences of the NHRs regarding their current medication regimen. NHRs and/or their family will be given the opportunity to receive feedback from the nurse or the GP on the issues discussed during the case conferences, and to get information on the treatment and the proposed changes. HCPs can agree to postpone the implementation of certain interventions until discussion with and agreement of the NHR and/or family. The HCPs are paid for each interdisciplinary case conference.

### Control group

Nursing homes allocated to the control group receive no intervention and continue delivering usual care. After completion of the last data collection, control NHs will have access to the e-learning platform and will have the option of attending a symposium that presents a summary of key messages relative to the effect of the intervention. They will also receive feedback on their own results relative to appropriateness of prescribing.

### Data collection

Data will be collected at three points in time: at month 1 (baseline), month 8 and month 15 (end of study). Data collection is performed by the HCPs involved in the care of each resident through a web application. Administrative and clinical data (e.g. age, functional status) are collected by the nurse, comorbidities (past and current medical history) and laboratory values by the GP, and medication data by the pharmacist. In the middle (month 8) and at the end of the study (month 15), data on health-care use (hospital admissions, emergency visits, GP or specialist visits) will also be collected by the nurse and the GP.

Characteristics of NHs (e.g. number of beds, location) and administrative data about participating HCPs are collected at the beginning of the study (month 1) from the coordinating physician and respective HCPs. HCPs will be paid for data collection.

In the intervention group, HCPs are also requested to record data on each case conference (participants, time for preparation, duration, DRPs identified, interventions,…)

Access to the web application is secured and requires both the national electronic identity card and the entry on a list of registered HCPs. HCPs have only access to data collection files of NHRs for which they are responsible. Data export from the web application to the research database will be performed with the intervention of a trusted third party (TTP), who is responsible for data coding and small cell analysis. NHRs and HCPs will be known to the research team by study ID number only. The whole process was approved by the Privacy Commission (nb 14/095, 21/10/2014).

For qualitative data (see ‘Process evaluation’ section), all interviews and focus groups will be audio recorded and transcribed verbatim, and the transcripts will be pseudo-anonymised.

### Outcomes

#### Primary outcome

The primary outcome measures relate to the appropriateness of prescribing at the resident level and are defined as (1) among residents who had at least one PIM/PPO at baseline, the proportion of them for whom there is a decrease of at least one of these PIM/PPO at the end of study and (2) among all residents, the proportion of them for whom at least one new PIM/PPO is present at the end of the study as compared to baseline.

PIMs/PPOs will be identified from a pre-defined list of explicit criteria that includes STOPP/START (version 2) [11] and Beers (2015) criteria [12]. To automatically identify PIMs and PPOs from the research database, the research team has developed and validated with GPs, geriatricians and pharmacists an algorithm for detecting STOPP/START criteria (version 2) and Beers criteria (2015).

### Secondary outcome measures

The secondary outcome measures include individual components of appropriateness of prescribing, medication use, the outcomes of the case conferences, clinical outcomes and costs. An overview of secondary outcome measures is provided in Table 2.

**Table 2 Tab2:** Secondary outcome measures and process evaluation

	Measure
Secondary outcome measures	
Appropriateness of prescribing, individual components	-Prevalence of PIM and PPO per criterion
Medication use	-Number of medications per NHR -Classes of medications used (ATC level 2 and 3)
Clinical outcomes	-Death -Hospital admissions -Visits to an emergency department -Visits to the GP and to specialist physicians
Outcomes of case conferences	-Type of identified DRPs -Type of planned interventions -Mean/median number of DRPs identified per NHR -Proportion of interventions implemented at the next case conference
Cost	-Cost of medication -Cost of healthcare use (hospital admissions, visits to the emergency department, GP visits, consultation with specialists) -Cost of intervention
Process evaluation	
Training	-Dose (number of module per profession,…) -Reach (rate of participation,…) -Experience with intervention (satisfaction survey)
Local concertation	-Fidelity (percentage of NHs that organised 2 local concertations,…) -Dose (number of local concertations per NH) -Reach (number of participating GPs who attended local concertation,…) -Experience with intervention (semi-structured interviews and focus groups)
Interdisciplinary case conferences	-Fidelity (percentage of NHRs for which 3 interdisciplinary case conferences were conducted,…) -Dose (median number of case conferences per NHR,…) -Reach (who attended case conferences,…) -Experience with intervention (semi-structured interviews and focus groups)
Context of the NH	-Characteristics of NHs and HCPs -Context in which the intervention is being implemented (semi-structured interviews)

*PIM* potentially inappropriate medication, *PPO* potentially prescribing omission, *NHR*(s) nursing home resident(s), *GP* general practitioner, *NH*(s) nursing home(s), *DRP*(s) drug-related problem(s), *HCPs* health-care professionals

#### Process evaluation

MRC guidance for complex intervention studies recommends that process evaluations must be conducted within the trial to assess the implementation of the intervention, to clarify causal mechanisms and to identify contextual factors associated with variation in outcomes [30]. These three aspects (i.e. implementation, causal mechanisms and contextual factors) will be evaluated during the COME-ON study (see Table 2). For the implementation evaluation, we will evaluate (1) fidelity, which is the quality of the implementation, and whether the intervention was implemented as intended in the protocol; 2) dose, which is the number of components of the intervention that was delivered; and 3) reach, which is the extent to which the target audience came into contact with the intervention.

A combination of quantitative and qualitative methods (i.e. mixed-method approach) will be used. The qualitative process evaluation will be conducted through interviews or focus groups with a purposive sample of HCPs to explore their views on the acceptability, effectiveness, barriers and facilitators of the intervention. Interview guides will be developed and piloted.

### Sample size

Estimations of sample size calculations were performed for the two primary outcomes.First, we estimated that among residents who had at least one PIM/PPO at baseline, there would be a decrease of at least one of these PIM/PPO at the end of the study for 20 % of NHRs in the control group and 40 % in the intervention group. We considered a power of 80 % and a statistical significance of 5 %. To take into account, the cluster nature of the study, we inflated the standard sample size estimates by a factor, i.e. the design effect = 1 + *ρ*(*m* − 1), where *m* is the average cluster size and *ρ* is the estimated intracluster correlation coefficient (ICC) [31]. As Belgian data on the ICC for the primary outcome measure were not available, we made estimations for two extreme values, i.e. 0.05 and 0.5. In fact, based on what has been found in the other primary care research setting, the ICC can be reasonably estimated between 0.05 and 0.5. With an average cluster size of 30 NHRs and an estimated percentage of dropouts of 22 %, a total of number of 502 and 3175 NHRs will be required for ICC values of 0.05 and 0.5, respectively.Second, we estimated that among all residents, there would be at least one new PIM/PPO present at the end of the study as compared to baseline for 20 % of NHRs in the control group and 10 % in the intervention group. Similarly to the estimation for the first outcome, we considered two extreme values of ICC, i.e. 0.05 and 0.5. With an average cluster size of 30 NHRs and an estimated percentage of dropouts of 22 %, a total of number of 1223 and 7738 NHRs will be required.

As mentioned above, the funding body (NHIDI) determined a priori the number of NHs and NHRs for the COME-ON study. Based on the previous cluster studies, we can expect an ICC closer to 0.05 than 0.5; consequently, a total of approximately 1890 NHRs might be enough to detect a statistically significant difference.

### Data analysis

#### Quantitative analysis

Data from the trial will be analysed and reported in accordance with the CONSORT criteria. The baseline characteristics will be reported as mean (± standard deviation) or median (and P25; P75) values for continuous variables and as counts (percent) for categorical variables. Descriptive statistics will be used to evaluate differences between intervention and control group on baseline characteristics at the resident, physician and nursing home level. Continuous variables will be compared using Student *T* test or Wilcoxon rank-sum test for clustered data, as appropriate. Categorical variables will be compared using adjusted chi-square test for clustered data.

To assess the impact of the intervention on the primary outcomes, logistic regression will take into account the complex design issues of the study (clustering, stratification). A multivariable model will be built to adjust the analysis for potential confounders, i.e. the number of PIMs/PPOs at baseline per resident and other baseline characteristics of residents, GPs and NHs. The analysis will be conducted using the intent-to-treat analysis, i.e. all residents will be analysed as randomised. A per protocol analysis will also be performed as a secondary analysis.

The impact of the complex intervention on the secondary outcome measures will be assessed using descriptive data and in some cases, using appropriate statistical evaluation.

Data analysis will be performed using R software (Free Software Foundation, Inc., Boston, MA, USA). A *p* value <0.05 will be considered statistically significant.

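### Two primary outcomes share one effectiveness objective, each at the full 5%, with no joint rule: if either may carry the claim, two-sided family-wise error is up to about 9.75%

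*Protocol article*

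**What the plan says.** The Objectives section of the protocol article gives a single primary objective: the effectiveness of the intervention on appropriateness of prescribing. The Primary outcome section then defines two measures:

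- Outcome 1, where higher is better: "among residents who had at least one PIM/PPO at baseline, the proportion of them for whom there is a decrease of at least one" of those items at the end of the study.
- Outcome 2, where lower is better: "among all residents, the proportion of them for whom at least one new PIM/PPO is present at the end of the study", compared with baseline.

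The Sample size section treats them separately: "Estimations of sample size calculations were performed for the two primary outcomes". For outcome 1 it states: "We considered a power of 80 % and a statistical significance of 5" per cent. The assumed rates are "for 20 % of NHRs in the control group and 40 % in the intervention group" for outcome 1 and "for 20 % of NHRs in the control group and 10 % in the intervention group" for outcome 2. For the ICC, "we made estimations for two extreme values, i.e. 0.05 and 0.5". The section concludes that about 1890 residents might suffice, without saying for which outcome.

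The Quantitative analysis section plans logistic regression for the primary outcomes and ends with one general criterion, a p "value <0.05 will be considered statistically significant". The article gives no order of testing, no split of alpha, no requirement that both succeed, and no guidance for results that disagree.

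**The concern.** With two primary outcomes and one claim, the trial's error rate depends on how the two tests are combined. The article fixes the threshold for each test but not the combination. A reader of the final report could treat one significant primary outcome as showing effectiveness, and nothing in the article would contradict that. The type I error of the headline claim would then exceed the nominal level.

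The outcomes can also disagree. Outcome 1 credits a resident for whom one baseline item is resolved, whatever else is added; outcome 2 counts new items separately. One resident can therefore be a success on the first and a failure on the second. Case conferences may lead to drugs being added, stopped or replaced, so opposite movement is possible. The results are meant to inform policymakers, so how a mixed result will be read should be settled before the data are seen.

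**Working it through.** **Inputs.** Sample size section: rates 20% vs 40% (outcome 1) and 20% vs 10% (outcome 2), power 80%, significance 5%, average cluster size 30, dropout 22%, ICC 0.05 or 0.5, about 1890 residents available. Sidedness is not stated. The correlation between the two test statistics is not in the article, so a range is assumed.

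**Step 1: reproduce the stated sample sizes.** Arcsine formula with two-sided 5% and equal arms: n per arm = 2(1.960 + 0.842)² / h², where h = 2|asin√p1 − asin√p2|. Total = 2n × [1 + ρ(30 − 1)] / (1 − 0.22). The design effect is 2.45 at ICC 0.05 and 15.5 at ICC 0.5.

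| Outcome | h | n per arm | Total, ICC 0.05 (stated) | Total, ICC 0.5 (stated) |
|---|---|---|---|---|
| 1 | 0.442 | 80.3 | 504 (502) | 3191 (3175) |
| 2 | 0.284 | 194.9 | 1224 (1223) | 7746 (7738) |

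The pooled-variance formula gives 515 and 3259 for outcome 1, and 1250 and 7909 for outcome 2, all within 3% of the stated values. A one-sided 5% gives 402 and 986 at ICC 0.05 and does not fit. So each outcome was sized with the full two-sided 5%; no alpha was shared.

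**Step 2: error if either outcome suffices.** For independent tests, 1 − 0.95² = 0.0975; the upper bound for any dependence is 0.05 + 0.05 = 0.10. For bivariate normal statistics with correlation r:

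| r | Any false significant result, either direction | Any false result favouring the intervention |
|---|---|---|
| 0 | 9.75% | 4.9% |
| 0.5 | 9.1% | 4.5% |
| 0.7 | 8.4% | 4.2% |
| 0.9 | 7.0% | 3.5% |

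The first column depends only on the size of r. At r = −0.5 the favourable column is 5.0%, its upper bound. A single two-sided 5% test has 2.5% in the favourable direction.

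**Step 3: error if both must be significant.** The probability that both tests reject cannot exceed that of either one alone, so it is at most 5%. No adjustment is needed.

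**Step 4: cost of adjusting.** The harshest step of Holm tests at 0.025. Replacing 1.960 by 2.241 in Step 1, totals at ICC 0.05 are 611 (arcsine) to 622 (pooled) for outcome 1, and 1483 to about 1521 for outcome 2. Both are below 1890.

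Power with 1890 residents: effective n per arm = 1890 × 0.78 / design effect / 2, which is 301 at ICC 0.05 and 189 at ICC 0.10 (design effect 3.9).

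| ICC | Outcome | Power at 0.05 | Power at 0.025 |
|---|---|---|---|
| 0.05 | 1 | above 99% | above 99% |
| 0.05 | 2 | 93–94% | 89% |
| 0.10 | 1 | 99% | 98% |
| 0.10 | 2 | 78–79% | 69–70% |

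Ranges span the pooled and arcsine formulas. The outcome 1 rows count all 1890 residents, although that outcome is limited to residents with at least one item at baseline. Its margin is wide: even half of 1890, 945, exceeds 622.

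If both outcomes must succeed at 0.05, joint power at ICC 0.05 is at least 1 − 0.068 − 0.0003, or about 93%, on the same basis.

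**The case against.** Four points can be made for the plan.

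1. **The error figure can be misread.** A reader might infer that the chance of falsely declaring the intervention effective is 9 to 10%. It is not. That figure counts false findings of harm as well as of benefit; the favourable part is about 4.5 to 5%. This stands, and the two numbers must be kept apart.

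2. **The article does not say that one outcome is enough.** A threshold for each test is not a rule for trial success, and the two outcomes are listed together as the primary measures. If both are required, there is no inflation. This also stands: the excess error is conditional on the either-outcome reading. But the article does not adopt the other reading either.

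3. **Multiplicity rules often sit in an analysis plan, which is not shown.** Silence alone would be no finding. Here, however, the article commits itself: one objective, two primary outcomes, each sized at the full 5%, and one threshold for everything. Followed as written, it leaves the error rate of the claim undetermined.

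4. **Outcome 2 is itself the safeguard.** Because new items are a primary outcome, a rise would appear as an adverse primary result. A reader might infer that the plan allows success to be declared on outcome 1 while outcome 2 worsens. The article does not say that. It only fails to say how such a pair of results would be interpreted, so the point is limited to that gap.

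**Conclusion.** The concern holds in conditional form. If significance on either primary outcome supports the effectiveness claim, the two-sided family-wise error is up to about 9.75%, and the chance of a false favourable claim is about 4.5 to 5% rather than 2.5%, for correlations up to 0.5 in size. At higher positive correlation both are smaller. If both outcomes must be significant, the error stays within 5%. The article fixes neither reading, nor how discordant results will be interpreted.

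The figures assume two-sided tests, which the reproduced sample sizes support though the text does not state them, and approximately bivariate normal test statistics. The correlation range is an assumption. The remedy is affordable at the ICC of 0.05 that the authors expect to be nearer the truth, and less comfortable for outcome 2 if the ICC is 0.10.

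**What to change.** State one of two rules before end-of-study data are analysed:

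- **Either outcome may support the claim:** test the two primary outcomes with the Holm procedure at a two-sided family-wise 5% (smaller p-value against 0.025; if significant, the other against 0.05).
- **Both are required:** state that effectiveness is claimed only if both are significant at two-sided 0.05 in favour of the intervention.

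Under either rule, add that both outcomes are always reported and interpreted together, with 95% confidence intervals, and that a gain on outcome 1 accompanied by a worsening on outcome 2 is not presented as an overall improvement in appropriateness.

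No change to design or sample is needed. Under Holm, outcome 2 power falls at worst from about 93% to 89% at ICC 0.05, and from about 79% to 70% at ICC 0.10. The loss is smaller whenever outcome 1 is significant first, since outcome 2 is then tested at 0.05. The cost of the second rule is that a real effect confined to one outcome could not support the claim.
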